# Transcutaneous electrical acupoint stimulation for stage 1 hypertension: protocol for a randomized controlled pilot trial

**DOI:** 10.1186/s13063-020-04493-x

**Published:** 2020-06-22

**Keywords:** Transcutaneous electrical acupoint stimulation (TEAS), Lifestyle education, Stage 1 hypertension, Randomized controlled trial

## Abstract

**Background:**

Hypertension is a major pathogenic factor of cardiovascular diseases. Insufficient blood pressure control rate and sub-optimal medication adherence remain challenges for effective management of hypertension. Transcutaneous electrical acupoint stimulation (TEAS) has been used to treat various diseases, including hypertension, but the scientific evidence for its benefit remains insufficient. Therefore, we will perform a randomized, controlled clinical trial in patients with stage 1 hypertension to evaluate the effect of TEAS.

**Methods/design:**

The study will be a two-arm parallel, randomized controlled trial. Sixty patients with stage 1 hypertension will be randomly assigned to the TEAS group and the control group in a 1:1 ratio. The participants in the TEAS group will receive non-invasive acupoint electrical stimulation for 30 min at four acupoints in the upper and lower extremities at home, 4 times weekly for 12 weeks for a total of 48 sessions. Participants in the control group will not receive any form of acupoint stimulation. All participants in both groups will receive lifestyle education on how to control high blood pressure, including diet, weight control, and exercise. The primary outcome measure will be the change of the mean systolic blood pressure from baseline to 12 weeks. Secondary outcomes include the change of mean diastolic blood pressure, quality of life, body mass index, and physical activity level.

**Discussion:**

This pilot, randomized, controlled trial will explore the feasibility of TEAS. It will also provide potential clinical evidence for the efficacy and safety of TEAS in the treatment of patients with stage 1 hypertension. The results of this study will be published in peer-reviewed journals. Furthermore, this pilot trial as the precursor of a large scale randomized controlled trial will inform the sample size of the subsequent trial.

**Trial registration:**

Chinese clinical trial registry, ChiCTR1900025042, Registered on 8 August 2019 (http://www.chictr.org.cn/showproj.aspx?proj=41496).

## Background

Hypertension is a major risk factor for cardiovascular disease death and its global burden is increasing [1]. Stage 1 hypertension is a systolic blood pressure (SBP) of 140–159 mmHg or diastolic blood pressure (DBP) of 90–99 mmHg and is one of the common subtypes of hypertension in China [2]. Previous studies have shown that a 10-mmHg reduction in SBP or a 5-mmHg reduction in DBP significantly reduces the relative risk of coronary heart disease [3], and blood pressure (BP) control in patients with stage 1 hypertension below 140/90 mmHg also significantly reduced the risk of stroke or death [4]. Therefore, it is necessary to the adequately control BP in patients with stage 1 hypertension.

At present, the treatment of hypertension includes the use of antihypertensive drugs and lifestyle interventions [5]. A systematic review showed that drug treatment is ineffective for many patients with stage 1 hypertension [6]. Therefore, widely used lifestyle changes, including weight loss, reduced sodium intake, regular physical exercise, smoking cessation, and moderate alcohol consumption, are also important [7, 8]. However, the benefits of lifestyle interventions on blood pressure will decrease over time [9, 10]. Therefore, a sustainable and effective long-term non-drug treatment is needed [11].

Acupuncture is an important part of traditional Chinese medicine therapy and has proven antihypertensive effect in hypertensive patients [12–15]. However, some patients worry about the economic cost of acupuncture or the time it takes to get to the hospital to have it [16, 17]. Transcutaneous electrical acupoint stimulation (TEAS) is a new non-invasive acupuncture treatment, which combines the effects of transcutaneous electrical nerve stimulation (TENS) with acupoint stimulation [18]. It stimulates the afferent nerves with low-voltage pulses transmitted through the skin at an acupoint, and TEAS may have a better antihypertensive effect than traditional acupuncture. In a study, Jacobsson et al. found that TEAS may have additional antihypertensive effect on 24-h ambulatory BP in those patients who did not respond to pharmacological treatment [19]. But it had some limitations, including the low quality of the study design and inadequate control groups. There are no randomized controlled trials to evaluate the efficacy of TEAS in the treatment of stage 1 hypertension at the present time.

In this study, we hypothesize that TEAS has an additional antihypertensive effect on stage 1 hypertension patients after lifestyle interventions. The results derived from this study will be used to explore the efficacy and safety of TEAS in lowering BP and calculated the appropriate sample size for a future large clinical trial.

## Methods/design

### Study design

This open-label, two-armed, randomized, controlled pilot trial will be conducted at Nanyuan Community Health Service Center which is one of chronic disease management bases in Beijing, China. The protocol has been registered on Chinese clinical trial registry (No ChiCTR1900025042) and approved by the ethics committee of Beijing University of Chinese Medicine (No 2019BZHYLL0208). The protocol follows the Declaration of Helsinki and will be reported in accordance with the Standard Protocol Items (SPIRIT) (Additional file 1).

### Study setting, recruitment

The clinical research coordinator will recruit 60 patients with stage 1 hypertension at Nanyuan Community Health Service Center in Beijing. The main recruitment strategies include the community’s chronic disease management software, WeChat advertisements, and on-site flyers at the outpatient department. The clinical research coordinator will conduct preliminary information screening by telephone or face to face. Then, patients who pass the preliminary screening will undergo a blood pressure test to determine whether they will be finally included. Written informed consent will be obtained by the clinical research coordinator at the outpatient department before randomization. Figure 1 shows the flow diagram of the trial.

**Fig. 1 Fig1:**
[figure not shown]
Flow diagram

### Participants

#### Inclusion criteria

Aged between 35 and 65 years (male or female)Fulfilling the diagnostic criteria for stage 1 hypertension (SBP of 140–159 mmHg and/or DBP of 90–99 mmHg) [20]Capacity to consent to taking part in the study and complete the questionnaires.Voluntary signing of informed consent

#### Exclusion criteria

Contraindications for the use of acupoint stimulators: wearing a pacemaker and other implanted medical devices; suffering from acute diseases, infectious diseases, malignant tumors; cardiovascular disease, cerebrovascular disease, liver and kidney dysfunction, or other malignant diseases; scars, bruises, scratches, or inflammation on the skin of the acupuncture points.Secondary hypertension caused by other vascular diseases, primary aldosteronism, other endocrine hypertension, etc.Receiving drugs that affect blood pressure except antihypertensive drugs in previous 2 months such as glucocorticoids, central nervous system inhibitors.Uncontrolled diabetes.Drug or alcohol abuse.Pregnant women or women in lactation period.Acupuncture treatment within the past month.Participation in another clinical study in the past month.

### Randomization and masking

Eligible patients will be randomly assigned to the TEAS group or control group in a ratio of 1:1. The randomization sequence will be generated with the software SAS 9.3 by an independent statistician ([name], Beijing University of Chinese Medicine, China) using block randomization. Randomization sequence will be stored by a non-involved investigator. When an eligible patient needs to be randomized, the clinical research coordinator will contact the non-involved investigator by phone to obtain random number and assign him/her to one group. The design is open label, but the outcome assessors and statisticians who are blinded to group allocation will be responsible for collecting and analyzing the data, respectively.

### Interventions

The physician will provide lifestyle education to all patients for 12 weeks, which mainly includes sending relevant antihypertensive information to patients every week and holding health lectures every month. The content of the information includes influence of lifestyle on hypertension control, especially the strength of dietary health, and the importance of moderate physical exercise, maintaining normal weight and quitting smoking. In addition, we will establish a communication group to answer questions raised by patients during the intervention. If patients were on antihypertensive medication, they were instructed to continue this medication but to abstain from changing the type or dosage of drugs.

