### Sample size

This is a pilot trial, and the sample size is based on the minimum sample size of clinical trials. Each group will include 30 participants, a total of 60 participants. This is the minimum number of participants used for comparative analysis to determine the initial data of main outcome measurements and explore for future large-scale randomized controlled trial [30].

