### Statistical analysis

Statistical analysis will be conducted by SPSS version 23.0 (IBM SPSS Statistics, NY, USA). Intention-to-treat analysis (ITT) will be applied to all cases randomly assigned to each group [31]. We will try our best to collect the data for the patients who quit or lost the visit in this trial. The last observation carried forward (LOCF) will be used for missing data. There is no interim analysis or additional analysis in this trial. The level of significance will be established at *α* < 0.05 with a two-sided test. Patients’ baseline characteristics will be described for the two groups. Continuously distributed variables will be described using mean ± standard deviation (M ± SD) or median and quartile intervals. Discrete variables will be described by frequencies and percentages. For the primary outcome, the change in SBP between baseline and 12 weeks after treatment will be calculated and the difference of the change in SBP between the two groups will be tested using Student’s *t* test or the Wilcoxon rank sum test. For secondary outcomes, Student’s *t* test, chi-squared test, Fisher’s exact test, or the Wilcoxon rank sum test will be used to test the difference of the outcomes including the DBP, BMI, IPAQ, and SF-12, between groups according to the distribution of variables.

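### The primary SBP analysis cannot use antihypertensive drug use at entry, which gives up a little precision and some planning information for the next trial

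*Protocol article*

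**What the plan says.** Entry is defined by one range for everyone: "Fulfilling the diagnostic criteria for stage 1 hypertension (SBP of 140–159 mmHg and/or DBP of 90–99 mmHg". It does not separate readings taken on treatment from readings taken off it. The drug exclusion explicitly spares antihypertensives: "Receiving drugs that affect blood pressure except antihypertensive drugs in previous 2 months". Under Interventions, users stay on their drugs in both arms: "If patients were on antihypertensive medication, they were instructed to continue this medication but to abstain from changing the type or dosage of drugs". One of the main recruitment routes is a chronic disease register ("The main recruitment strategies include the community’s chronic disease management software"), so drug users can be expected, although the article does not give their share.

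On size: "Each group will include 30 participants, a total of 60 participants". On analysis, the Statistical analysis section states that for the primary outcome "the difference of the change in SBP between the two groups will be tested using" a t test or a rank sum test. No covariate is named, and the same section rules out interim and further analyses.

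The article also says, in the Abstract and at the end of the Background, that the results will be used to size a larger trial. The Discussion describes the target population in more than one way. It speaks of patients who decline drugs or take them poorly, of postponing drug treatment, and of a later real-world trial of TEAS added to other treatment.

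**The concern.** Drug use at entry is available without extra effort, because screening must take a drug history to apply the exclusion criteria. It could also predict the outcome. Type and dosage are frozen, but adherence is not. The Abstract names poor adherence as a problem, and both arms receive weekly material on blood pressure control. Better adherence can lower SBP only in patients who have a drug to take. Whether this happens, and by how much, is not stated anywhere.

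Because the article fixes an unadjusted test and excludes further analyses, the omission is a stated choice and not a detail left to an unseen analysis plan. Two things are at stake. If 12-week change differs between users and non-users, some precision is given up. And a pilot meant to size a later trial would report one SD of change, while the article leaves open whether that trial is for patients putting off drugs, for add-on use, or for both.

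**Working it through.** **Inputs from the article.** 30 per arm (30 + 30 = 60, which agrees with the stated total); two-sided 0.05; primary outcome is SBP change from baseline to 12 weeks. The article gives no effect size, SD, power or share on drugs, so no power figure can be reproduced.

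**Assumptions.** Share on drugs p = 0.5; SD of change within each drug-use group 10 mmHg; gap g in mean 12-week change between users and non-users of 0, 3, 5 or 8 mmHg; later trial sized for 5 mmHg with 80% power.

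**Step 1: chance imbalance.** The SD of the difference in drug share between arms is √(2p(1−p)/30) = √(0.5/30) = 0.129. With two independent Binomial(30, 0.5) counts, a difference of 20 points or more has probability 0.155 (0.12 at p = 0.3 or 0.7). It moves the observed SBP difference by 0.20 × g, that is 0.6, 1.0 or 1.6 mmHg for g = 3, 5, 8. The move has random sign.

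**Step 2: does this invalidate the test?** In 40,000 simulated null trials per gap, mean bias was within 0.02 mmHg and the type I error of the unadjusted t test was 0.050 at every gap. With adjustment for drug use (8,000 trials each) it was 0.048 to 0.053.

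**Step 3: precision and planning.** Pooled SD = √(10² + 0.25g²). The unadjusted standard error is pooled SD × √(2/30) by formula. The table gives the simulated values, which agree to about 0.01. The later trial needs n per arm = 2(1.960 + 0.842)² × SD²/5².

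| g (mmHg) | Pooled SD | Excess over 10 | SE unadjusted | SE adjusted | n per arm, pooled SD |
|---|---|---|---|---|---|
| 0 | 10.00 | 0% | 2.59 | 2.63 | 63 |
| 3 | 10.11 | 1.1% | 2.61 | 2.60 | 65 |
| 5 | 10.31 | 3.1% | 2.65 | 2.60 | 67 |
| 8 | 10.77 | 7.7% | 2.77 | 2.59 | 73 |

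The loss at g = 0 is 2.63 − 2.59 = 0.04 mmHg. Part of this is simulation noise: 2.63/√(2 × 8,000) ≈ 0.02. The adjusted standard error should not depend on g, and the four adjusted values average 2.60, so the true cost is nearer 0.02. These figures isolate drug use; adjustment for baseline SBP is not included.

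**Step 4: unequal SDs.** With SDs of 8 and 12 in the two groups and g = 3, pooled SD = √(0.5 × 64 + 0.5 × 144 + 0.25 × 9) = 10.3, giving 67 per arm. A trial restricted to one group would need 41 (SD 8) or 91 (SD 12).

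**Step 5: what reporting by drug use can deliver.** At p = 0.5 there are about 15 per arm in each group, so the standard error of the SBP difference is 10 × √(2/15) = 3.7 mmHg. At p = 0.3 the smaller group has about 0.3 × 30 = 9 per arm and a standard error of 10 × √(2/9) = 4.7 mmHg.

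**The case against.** The best defence is that nothing here is an error. Imbalance in drug use under randomization is random variation that the standard error already covers, and the same could be said of age, sex or BMI. The outcome is a change, with drug type and dosage held constant, so a difference in SBP level between users and non-users cancels. Only a difference in change matters, and the article gives no evidence of its size. Even a 20-point imbalance shifts the result by 0.6–1.6 mmHg against a standard error of 2.6–2.8. The planning effect is also modest: an SD estimated from 60 patients has a relative error of about 1/√(2 × 58) = 9%, larger than the 1–8% excess.

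All of that stands, and it rules out three stronger readings that a reader might infer.

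- *That chance imbalance biases the estimate.* It does not: bias is nil on average and type I error is unchanged.
- *That the pooled SD describes neither users nor non-users.* With equal SDs it is close to both, and for a later trial with the same mix and an unadjusted comparison it is the correct SD.
- *That allocation is unstratified.* The article says only that allocation is 1:1, "using block randomization". A condensed article commonly leaves stratification factors to the full protocol, which is not at hand.

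The defence does not dispose of the analysis choice itself. The article states the unadjusted test and closes off any alternative, although the variable is known at entry and using it costs almost nothing.

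**Conclusion.** The point holds as a low-cost improvement in efficiency and planning. The documents establish that users and non-users are pooled, that the primary test ignores drug use, and that further analyses are excluded.

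The gain depends on an unknown gap in 12-week change. It is negligible at 3 mmHg, small at 5 and visible only at 8. Without a gap there is a slight loss. The 3–8 mmHg range, the SD of 10 and the 50% share are assumptions without support in the article.

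For planning, the single SD would mislead materially only if the SDs of users and non-users differ clearly, or if the later trial is restricted to one of the two populations. The Discussion leaves the second possibility open, which is the main reason to report the SD by drug use.

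**What to change.** 1. In Statistical analysis, replace the two-group test for the primary outcome with a linear model for 12-week SBP that includes treatment group, baseline SBP and antihypertensive use at entry (yes/no). The t or rank sum test can stay as a supporting analysis.
2. State there that the SD of SBP change and, descriptively, the SBP difference will be reported by drug use at entry. Add that with about 15 per arm or fewer in each group these estimates are imprecise and do not show for whom TEAS works. Amend the sentence that excludes further analyses to allow this.
3. Reconcile the population wording in Interventions with that in the Discussion, so that the pilot's population and the later trial's population are stated once and consistently. Which population is intended is a clinical decision for the investigators.

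Cost: one degree of freedom for drug use and one for baseline SBP, and a slight loss of precision if drug use does not predict change. No extra patients, visits or measurements are needed. Trial status reports 30 patients randomized and follow-up to October 2020, so the analysis text could still be changed before the data are analysed.

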#### Control group

Subjects randomized to the control group will not be given TEAS treatment except the lifestyle education.

#### Transcutaneous electrical acupoint stimulation group

In addition to the lifestyle education, the participants in this group will receive TEAS 48 sessions over a period of 12 weeks (4 sessions/week) at home. TEAS will be performed using a portable instrument for low-frequency electrotherapy (SDP-330, Yuwell, Suzhou Medical Appliances Co, Ltd., Suzhou, China). The device is a so-called dual channel stimulator with two pairs of rubber electrodes (30 mm × 30 mm) applied to the skin as illustrated in Fig. 2. The instrument has 8 different stimulus modes; patients will be asked to select a fixed mode (“press” or “knock” or “knead” mode) throughout the trial. It has ten different stimulus intensities, and patients could choose based on their tolerance.

**Fig. 2 Fig2:**
[figure not shown]
Locations of acupoints

According to the previous studies [21, 22], bilateral Hegu (LI4), Quchi (LI11), Zusanli (ST36), and Taichong (LR3) will be selected in our trial. At the first session, the electrodes will be placed at the ipsilateral LI4 and LI11, and then the appropriate stimulus intensity will be selected according to tolerance of each individual for 15 min after connecting the instrument, then the opposite limb will be treated in the same way for 15 min. In the second session, the ST36 and LR3 acupoints of the leg will be treated for 15 min in the same way. Two pairs of acupoints will be stimulated alternatively every other day. Locations of acupoints are shown in Table 1.

**Table 1 Tab1:** Locations of acupoints in the TEAS group

Acupoints	Locations^a^
Hegu (LI4)	On the dorsum of the hand, radial to the midpoint of the second metacarpal bone.
Quchi (LI11)	On the lateral aspect of the elbow, at the midpoint of the line connecting LU5 with the lateral epicondyle of the humerus.
Zusanli (ST36)	On the anterior aspect of the leg, on the line connecting ST35 with ST41, 3 B-cun inferior to ST35. ST36 is located on the tibialis anterior muscle.
Taichong (LR3)	In the depression anterior to the junction of first and second metatarsal bones.

^a^1 cun (≈ 20 mm) is defined as the width of the interphalangeal joint of patient’s thumb

The acupuncturist will train the participants on how to locate the acupoints and use the instrument face-to-face. They will also send paper instructions and acupoint maps to help patients with TEAS treatment at home. The patients will be required to record the date, the time, and the specific acupoints when using the instrument. The instrument will be given to the patients when they have completed the prescribed treatment times and visits.

### Outcomes

#### Primary outcome

The primary outcome of the study is the change in mean SBP between baseline and 12 weeks after treatment. BP will be measured and recorded by using an electronic sphygmomanometer (HEM-7136, Omron Corporation, Kyoto, Japan) in both groups. Patients were asked to rest quietly for at least 5 min before taking blood pressure measurements of the upper arm in the sitting position, with the upper arm at heart level [23]. Blood pressure in both upper arms should be measured at the first test; the side with the higher blood pressure reading will be selected. At subsequent detection time points, the measurement will be repeated 3 times every 5 min; the average value of the last 2 readings will be taken as the mean BP [24].

#### Secondary outcomes

The mean SBP will be evaluated at weeks 24 and 36 after randomization. The mean DBP, body mass index (BMI), International Sports Activity Questionnaire (IPAQ), and Short Form (SF-12) will be evaluated at baseline, 12 weeks, 24 weeks, and 36 weeks. The DBP measurement method is consistent with SBP. BMI is weight (kg) divided by the square of height [25, 26]. The IPAQ questionnaire includes the frequency, intensity, timing, and type of exercise [27], which will be divided into three levels of physical activity levels by metabolic equivalent (MET). The SF-12 is a questionnaire to evaluate general health outcomes including psychological and physical domains [28, 29].

The schedule of enrolment, intervention, and assessments is shown in Fig. 3.

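### IPAQ is reduced to three activity levels although its MET value must be computed first; this costs power, and more if the open choice of test falls on an unordered one

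*Protocol article*

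**What the plan says.** Under Secondary outcomes, the protocol article lists IPAQ at baseline and at 12, 24 and 36 weeks. It describes the questionnaire as one "which will be divided into three levels of physical activity levels by metabolic equivalent (MET"). The abstract likewise names physical activity level as the secondary outcome. No continuous MET outcome appears anywhere.

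Under Statistical analysis, one sentence covers all secondary outcomes. Besides Student's t test it names "exact test, or the Wilcoxon rank sum test will be used to test the difference of the outcomes including the DBP, BMI, IPAQ, and SF-12", with the choice made "between groups according to the distribution of variables". No test is tied to a named outcome. The significance level is "< 0.05 with a two-sided test".

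Under Sample size: "Each group will include 30 participants, a total of 60 participants". The basis is given as "This is a pilot trial, and the sample size is based on the minimum sample size of clinical trials", with no effect size, SD or power.

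**The concern.** Two separate losses of information are possible.

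- **Cutting.** A MET value is computed for each patient and then replaced by one of three levels. Two patients far apart on the MET scale can share a level, and two close together can be split. The text states this step.
- **Ignoring order.** The three levels are ordered. A chi-squared or Fisher's exact test treats them as unordered and spreads a directional shift over two degrees of freedom. The text permits this step but does not state it.

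What is at stake is the precision with which the trial can describe a difference in activity between the arms. Both arms receive exercise advice in an open-label design, so that description is useful. With 30 per arm there is little information to spare.

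**Working it through.** The document states no power for IPAQ, so there is no figure to reproduce. The check asks what each permitted analysis would give under stated assumptions.

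**Inputs from the document:** 30 per arm (Sample size); 1:1 allocation (Randomization and masking); two-sided 0.05 (Statistical analysis); three levels cut by MET (Secondary outcomes).

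**Assumptions, not in the document:** a normal latent activity score (for example a transformed MET value); a shift of d = 0.5 or 0.75 SD in one arm; and five control-arm splits over low/middle/high levels.

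**Step 1, benchmark on the continuous score.** With the normal approximation, power = Φ(d·√(n/2) − 1.96). For d = 0.5 and n = 30: 0.5 × √15 = 1.936, and Φ(1.936 − 1.960) = Φ(−0.024) ≈ 0.49. The exact t test gives 0.478 at d = 0.5 and 0.815 at d = 0.75.

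**Step 2, simulation.** There were 10,000 replicates per setting, so the Monte Carlo standard error is at most √(0.25/10,000) = 0.005. Each data set was analysed by Wilcoxon on the score, by Wilcoxon on the three ordered levels, and by Pearson chi-squared on the 2×3 table. With equal arms the last is X² = Σ(a − b)²/(a + b) over the levels, on 2 df, where a and b are the counts in the two arms. Fisher's exact test was not simulated; it also ignores the order.

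| Control split (%) | d | Wilcoxon, score | Wilcoxon, levels | Chi-squared, levels |
|---|---|---|---|---|
| 33/33/33 | 0.5 | 0.455 | 0.394 | 0.303 |
| 25/50/25 | 0.5 | 0.454 | 0.399 | 0.309 |
| 20/40/40 | 0.5 | 0.451 | 0.378 | 0.291 |
| 10/50/40 | 0.5 | 0.454 | 0.362 | 0.268 |
| 10/30/60 | 0.5 | 0.453 | 0.322 | 0.228 |
| 33/33/33 | 0.75 | 0.789 | 0.701 | 0.600 |
| 25/50/25 | 0.75 | 0.787 | 0.712 | 0.610 |
| 20/40/40 | 0.75 | 0.793 | 0.684 | 0.576 |
| 10/50/40 | 0.75 | 0.792 | 0.664 | 0.536 |
| 10/30/60 | 0.75 | 0.793 | 0.582 | 0.447 |

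With no shift, every test rejected in about 5% of replicates (0.047 to 0.053), so the comparison is fair.

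**Step 3, separate the two losses.**

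- Cutting alone (Wilcoxon on score minus Wilcoxon on levels): from 0.454 − 0.399 = 0.055 to 0.453 − 0.322 = 0.131 at d = 0.5; from 0.787 − 0.712 = 0.075 to 0.793 − 0.582 = 0.211 at d = 0.75.
- Ignoring order as well (Wilcoxon on levels minus chi-squared): from 0.378 − 0.291 = 0.087 to 0.322 − 0.228 = 0.094 at d = 0.5; from 0.701 − 0.600 = 0.101 to 0.582 − 0.447 = 0.135 at d = 0.75.

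Repeat runs, some with other cut points, moved the ends of the ranges by about a point. The rounded ranges quoted in the conclusion allow for that.

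**Step 4, skewness.** Raw MET values may be skewed, which would lower the t-test benchmark. Wilcoxon on the score is therefore the safer comparator. All three tests in the table are unchanged by a monotone transformation of the score if the cut points move with it, so the comparison needs only that some such transformation is roughly normal.

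**The case against.** The strongest reply is that the plan never assigns chi-squared to IPAQ. A reader might infer that it does, because IPAQ is the only listed secondary outcome described as categorical and chi-squared and Fisher's exact tests have no other evident use there. That is a natural reading, but it is not what the text says. Wilcoxon rank sum is on the same list and keeps the order, and assigning a test to each secondary outcome may properly be left to an analysis plan that is not shown. The sentence "Discrete variables will be described by frequencies and percentages" does not settle it, since it follows directly on the description of baseline characteristics and does not concern testing. This objection stands: loss of order is possible, not stated.

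It can also be said that reporting levels is a legitimate choice of outcome, that this pilot has no power target, and that nothing in the document turns on a significant IPAQ result. This also stands and limits the weight of the point. It does not remove the fact that a value already in hand is left out of the analysis.

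A reader might further infer that a weak IPAQ test leaves a systolic blood pressure difference open to explanation by changed activity, and that a stronger test would close the question. The documents do not support that. A between-arm significance test on either scale neither establishes nor excludes such an explanation; that would take the estimated difference with its interval, or a mediation analysis. The document also gives no basis for expecting an activity difference of 0.5 to 0.75 SD.

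**Conclusion.** The point holds in a limited form. The reduction of IPAQ to three levels is stated, and under the assumptions above it lowers power from about 45% to 31–40% at 0.5 SD and from about 79% to 58–72% at 0.75 SD, even with the best of the listed tests for ordered levels. If the unordered chi-squared test were chosen, power would be about 22–32% and 45–62%; that further loss is conditional on a choice the plan leaves open. The sizes depend on the assumed shifts, splits and normal latent score, while the ordering of the three analyses was the same in every setting examined. The severity is minor: a worthwhile improvement to a secondary outcome of a pilot, with no bearing on the primary analysis.

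**What to change.** State that IPAQ is analysed as total MET-minutes per week, by Wilcoxon rank sum or by ANCOVA on the rank or log scale with the baseline value as covariate. Present the three levels descriptively. If the levels are also tested, name an ordered method (Wilcoxon rank sum or a proportional-odds model) and exclude chi-squared and Fisher's exact tests for this outcome.

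The cost is wording only: the MET value is already computed to assign the levels, and IPAQ is already collected at baseline. Because the Statistical analysis section rules out additional analyses, the change should replace the current form of the outcome in the plan, and should be recorded before the IPAQ data are compared between arms.
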